**Methods:**

A prospective multi-centre randomised controlled trial (RCT) will be conducted in Obstetrics and Gynaecological units of five public hospitals in Hong Kong, China. Data will be collected from March 2016 onward for 2 years. The target population is Chinese women with an uncomplicated singleton pregnancy at gestational age of 37 to 42 weeks. Participants are randomised based on parity (nulliparous and multiparous) and type of labour onset (spontaneous and induced). Women in the intervention group are actively offered and taught how to use a birth ball; those in the control group receive the usual midwifery care. The target sample size is 512. The primary outcome measures are maternal pain intensity, satisfaction with pain relief, sense of control in labour, assisted delivery and satisfaction with childbirth experience. Labour pain relief is measured by visual analogue scale (VAS). Other outcomes will be measured through four different validated questionnaires. To control for potential cluster effects, a linear mixed model will be used. An intention-to-treat analysis is adopted and performed by researchers unknown to subjects’ group allocation.

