## Methods

A randomised controlled trial (RCT) is designed and the objective is to evaluate the effectiveness, safety and harm of birth ball use by pregnant women in labour compared to treatment as usual group. The research hypothesis is that participants randomised to the birth ball intervention group have better pain relief, higher satisfaction with pain control, higher sense of control in labour and higher satisfaction with childbirth experience, when compared to subjects in control group. This study protocol follows the SPIRIT checklist.

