### Sample size

Data to estimate sample size is only available from two randomised trials [13, 14]. Both trials have high risks of bias that likely lead to an overestimated effect size (Cohen’s d 0.90–1.34) in labour pain relief by birth ball, measured by visual analogue scale (VAS).

Without existing rigorous research enabling more accurate estimation of effect size, we re-calculated sample size with a conservative Cohen’s d of 0.25 in pain relief measured by VAS, alpha 0.05 and a power of 0.8. This was calculated using software G*Power (version 3.1.9.2). In order to have an equal number of participants in intervention and control groups, participants of each stratified block are further amended as 64 in each stratum. This gives a sample size of 512.

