### Outcome measurements

A Cochrane systematic review reported a list of core outcomes for labour pain control, agreed through a wide consultation with researchers and consumer groups [1]. These outcomes include many important clinical and patient-relevant measures relating to the mother and baby. The data is collected from participants’ medical record and questionnaire. A summary of the primary outcomes and corresponding measurements is listed in Table 1.

**Table 1 Tab1:** Summary of primary outcomes and measurements

Primary outcomes	Measurements
1. Pain intensity	Visual analogue scale (VAS)
2. Satisfaction with pain relief	American Pain Society – Patient Outcome Questionnaire–Modified (APS-POQ Modified)
3. Sense of control in labour	29-item Chinese validated Labour Agentry Scale (c-LAS)
4. Satisfaction with childbirth experience	Six Simple Questions (SSQ)

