#### Secondary outcomes

Other data we collect as secondary outcomes include effect (negative) on mother-baby interaction [25, 26], breastfeeding practices, delivery that require assisted vaginal birth and/ or Caesarean section, adverse effects of mother and infant, admission to special care baby unit or neonatal intensive care unit, five-minute Apgar score, and infant outcomes at longer term follow-up.

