### Statistical methods

Baseline characteristics of the two groups are compared by an ANOVA test for continuous variables and χ [2]-test for categorical variables. The primary outcomes are differences in the mean change of VAS pre- and post-intervention between birth ball and other control methods first on the list, and differences in total scores of APS-POQ modified, c-LAS and SSQ between groups. Secondary measures are differences in c-PBQ score and mode of delivery (assisted vaginal and caesarean); differences in proportions of breastfeeding, adverse effects, admission to special care baby unit or neonatal intensive care unit, five-minute Apgar score less than seven; and differences in cost.

To control for potential cluster effect, (e.g., participants by certain midwives) we will use a linear mixed model where the midwife is treated as a random effect. The basic model is a random intercept model with compound symmetry as the covariance structure. The data fitness is explored using alternative models, e.g., using different covariance structures, will be compared by the restricted maximum likelihood.

Intention-to-treat analysis is adopted and performed by researchers masked to subjects’ group allocation. A two-sided *P* value of 0.05 or less is considered statistically significant. Objective measures and clinical outcomes are validated independently by two researchers. To minimise missing data, research officers ensure complete data collection prior to subjects’ hospital discharge and remind subjects that a follow-up assessment takes place at 6 to 8 weeks post-partum.

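### Four primary outcomes share one unadjusted 0.05 threshold with no rule for a positive trial, while the sample size covers pain on the VAS alone

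*Protocol article*

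**What the plan says.** All references are to the protocol article.

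- **Number of primary outcomes.** Table 1 under Outcome measurements ("Summary of primary outcomes and measurements") has four rows: pain intensity on the VAS, satisfaction with pain relief, sense of control, and satisfaction with the childbirth experience. Statistical methods gives the same four: the VAS change, and "differences in total scores of APS-POQ modified, c-LAS and SSQ between groups". The closing paragraph of the Discussion lists the same four as the primary research questions.
- **Threshold.** Statistical methods sets one general criterion: a two-sided P "value of 0.05 or less is considered statistically significant". It is not divided or ordered across the four outcomes.
- **Hypothesis.** The opening of Methods expects the birth ball group to have "better pain relief, higher satisfaction with pain control, higher sense of control in labour and higher satisfaction with childbirth experience". It does not say how many of these must be shown.
- **Sample size.** The calculation uses a Cohen's d of 0.25 in "pain relief measured by VAS, alpha 0.05 and a power of 0.8" and arrives at 512. No other outcome enters it.
- **Abstract.** It lists five: "The primary outcome measures are maternal pain intensity, satisfaction with pain relief, sense of control in labour, assisted delivery and satisfaction with childbirth experience". The Secondary outcomes section places "delivery that require assisted vaginal birth and/ or Caesarean section" among the secondary measures, and Statistical methods does the same with mode of delivery.

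**The concern.** With several primary outcomes, a plan has to say what counts as success, because that choice sets both the false-positive rate and the power. Here four outcomes are primary and each can be called significant at 0.05, but the rule for combining them is absent. Two readings are open, and neither delivers 5% error together with 80% power. If one success is enough, the four tests together exceed 5%. If all four are needed, the chance of reaching that goal is lower than the 0.8 on which 512 was based.

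At stake is the headline claim. The Discussion says that favourable results would support policy and systematic introduction of the birth ball, but it does not define favourable. All four outcomes are the women's own reports. One isolated nominal result on a questionnaire could be presented as a positive primary finding, and the plan contains nothing against which to check that claim.

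**Working it through.** **Inputs.** From the document: four primary outcomes; two-sided threshold 0.05; d = 0.25 on VAS; target power 0.8; total 512, read as 64 per arm × 4 strata × 2 arms, which is 256 per arm. Assumed, because the document gives no figures: equal correlation ρ between the four test statistics, shown at 0, 0.5, 0.7 and 0.9; and, for joint power only, d = 0.25 on all four outcomes.

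**Step 1: reproduce the sample size.** For a two-sample t-test with d = 0.25, two-sided 0.05 and power 0.8, the solution is 252.1, so 253 per arm and 506 in total. Rounding up to 64 per arm in each stratum gives 512. With 256 per arm the power for VAS is 80.6%. The stated figure reproduces, and it uses the whole 0.05 on one outcome.

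**Step 2: any one success counts.** If no outcome has a true effect and the tests are independent, the family-wise error is 1 − 0.95⁴ = 18.5%. For correlated tests it is the probability that at least one of four equicorrelated normal statistics exceeds 1.96 in absolute value. Errors in the direction that favours the birth ball use a one-sided 0.025 per test; with independence that is 1 − 0.975⁴ = 9.6%.

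| Correlation | Either direction | Favouring the birth ball |
|---|---|---|
| 0 | 18.5% | 9.6% |
| 0.5 | 15.6% | 7.8% |
| 0.7 | 13.0% | 6.5% |
| 0.9 | 9.4% | 4.7% |
| One test only | 5% | 2.5% |

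**Step 3: all four must succeed.** Each test is then held at 0.05 and the overall error is not inflated. With 80.6% power on each outcome, joint power under independence is 0.806⁴ = 42%. With correlated tests it is 57% at 0.5, 63% at 0.7 and 71% at 0.9. Every value is below 0.8.

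**Step 4: can alpha simply be split?** Bonferroni gives 0.05/4 = 0.0125 per outcome and a family-wise error of at most 5% (1 − 0.9875⁴ = 4.9% if independent). VAS power with 256 per arm falls from 80.6% to 62.6%. Restoring 80% would take about 714 participants (normal approximation). An equal split is therefore not compatible with the sample size as calculated.

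**The case against.** The strongest reply is that this is a journal article. A multiplicity rule is often left to the full protocol or the analysis plan, and the 0.05 sentence may be no more than a general convention. That has weight: silence alone would not be a finding, and an adjustment may exist elsewhere. What remains is that the article itself fixes four primary outcomes, one undivided threshold and a sample size that gives the full 0.05 to one of the four. Step 4 shows that an unseen plan which split alpha equally would undercut the article's own power statement.

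A reader might infer that the trial carries a 13–19% chance of a false primary claim. The document does not support that as a plain statement. The rate applies only if any one success suffices, which is nowhere stated. It counts false results against the birth ball as well as for it. Its lower end depends on an assumed correlation of 0.7, and at 0.9 the figure is 9.4%. The hypothesis joins the four benefits with an *and*, and on that reading the error is not inflated at all.

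It is equally tempting to give 42% as the power for all four outcomes. That is the independence case; four self-reports from the same women are likely to be positively correlated, and the article gives no effect size for the questionnaires.

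A reader might also treat the abstract's fifth outcome as enlarging the primary family. Table 1, Secondary outcomes, Statistical methods and the Discussion agree on four, so this is an inconsistency between abstract and Methods and not a five-outcome design.

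Finally, keeping four primary outcomes with Holm, or with an explicit all-must-succeed rule, would also control error. That is true, but either would need its own power statement.

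**Conclusion.** The point holds as a gap between the four primary outcomes, the single threshold and the sample size. Under an any-one rule the family-wise error lies between 9.4% and 18.5% for correlations from 0.9 down to 0, about two to nearly four times the nominal 5%. Under an all-four rule the error is sound, but joint power lies between 42% and 71% over the same correlations, if every outcome has d = 0.25. The correlations and the questionnaire effect sizes are assumptions. The outcome count, the threshold and the VAS-only sample size are the document's own. Severity is moderate: the problem bears on how the main result may be claimed, but it is a missing decision rule that wording can supply, and the article does not commit to the reading with inflated error.

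**What to change.** Before unmasking, name the between-arm difference in VAS change as the single primary outcome at two-sided 0.05, since it is the only outcome that the sample size covers. Test APS-POQ Modified, c-LAS and SSQ as key secondary outcomes, by Holm or in a stated fixed order, and only if VAS is significant. This holds the family-wise error at 5%, keeps VAS power at about 80.6% and needs no further participants.

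The cost is a change of wording, and the three questionnaire outcomes lose their stand-alone primary status. The dates given for data collection (from March 2016, to the end of 2017 or for two years) precede publication in May 2019, so the data may already be unmasked. In that case, report the adjusted results and label the adjustment as post hoc.

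Separately, align the abstract with Secondary outcomes and Statistical methods on the status of assisted delivery.

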## Discussion

This study draws data from five different sites across Hong Kong, which will increase the generalizability of results and enable easier systematic adoption of the intervention in other non-trial units. With the large sample size, single-blinded and stratified randomisation design, the results we have will provide reliable data. We are using stratified randomisation according to potential confounders of parity (nulliparous or non-nulliparous) and type of labour onset (spontaneous or induced) – two strata give four possible combinations.

Taking ethical concerns into consideration, we are not forbidding women in the control group to use the birth ball if they request them, and vice-versa; we will not forcefully limit their other pain relief options. All the subjects from control group will remain in the control arm in the intention-to-treat analysis. This is regarded as a major limitation of the study that is not likely to be solved. Furthermore, since we aim to examine the effectiveness of the birth ball intervention as a whole in real clinical settings, these possible confounders are not intentionally separated out, as they are integral parts of birth ball application and implementation. Different hospitals have different cultures and settings, and hence this can lead to deviation in practice and therefore bias. To standardise the research protocol and administering of the intervention, meetings and training are given to the midwives at all study sites before and periodically during recruitment. There will be subgroup analysis in each hospital.

Other limitations of this study include the concomitant use of other non-pharmacological pain relief methods during labour. It is common for pregnant women to use several analgesic methods at the same time. Although the time and method of all the analgesic methods are noted, the outcome effects of using a birth ball would become difficult to measure. Besides, in a busy antenatal and labour ward, the completion of research data by midwives and staff would be less than expected. Our researchers follow-up each participant and ensure all the relevant information from the medical record is reviewed. Although it would be impossible to blind the midwives or physiotherapists who teach birth ball, all the researchers will not be disclosed the case or control status of participants in the ward and during data analysis.

Currently, birth balls are widely adopted in the delivery units in public and private hospitals in Hong Kong. Results from this study provide rigorous scientific evidence for policy development. If the results are favourable, it will facilitate systematic implementation to promote birth ball use for women in labour. Additionally, if proven effective and safe for mothers and babies, this simple non-invasive and non-pharmacological method can be used in delivery suites around the world, especially in low-resource settings at low cost to the healthcare system. Study results will be disseminated in peer-reviewed journals, academic and press conferences, and community conventions.

This study will be the largest RCT on birth ball use for pregnant women in the world, with a total of 512 subjects. Our primary research questions include the effect of using the birth ball on pain intensity, satisfaction with pain relief and childbirth experience, and sense of control in labour. Results will provide rigorous scientific evidence for clinical practice and policy development.

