### Study setting

Recruitment for the study is conducted in all three regions of Hong Kong to enhance the generalizability of the results: Hong Kong Island (Pamela Youde Nethersole Eastern Hospital); Kowloon (Princess Margaret Hospital, Kwong Wah Hospital and Queen Elizabeth Hospital); and the New Territories (Prince of Wales Hospital). The study was initiated in March 2016 and continues until the end of 2017. Figure 1 is a Consort flow diagram of the progress through the phases of a parallel randomised trial of the intervention and control group.

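### Separate subgroup analyses in each of five hospitals do not test whether the birth ball effect differs by site, and will probably give a mixed picture even if it does not

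*Protocol article*

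**What the plan says.** The trial recruits in "Obstetrics and Gynaecological units of five public hospitals in Hong Kong, China" (Abstract, Methods). Study setting gives the reason for the spread: "Recruitment for the study is conducted in all three regions of Hong Kong to enhance the generalizability of the results".

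The Discussion acknowledges that hospitals differ in culture and setup, and that this may lead to departures in practice and to bias. It gives two responses. The first is meetings and training for midwives at all sites, before and during recruitment. The second is analytic: "There will be subgroup analysis in each hospital".

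Statistical methods does not mention these hospital analyses. It sets one threshold with no exception for subgroups: "A two-sided *P* value of 0.05 or less is considered statistically significant". The only random effect it names is the midwife, although clustering by midwife is given as an example and alternative models are to be explored. Randomisation and strata lists parity and type of labour onset as stratification factors, and does not list hospital.

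Sample size plans for the overall comparison with "a conservative Cohen’s d of 0.25 in pain relief measured by VAS, alpha 0.05 and a power of 0.8". After rounding within strata: "This gives a sample size of 512".

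**The concern.** The question raised in the Discussion is whether differences between hospitals alter the result. That is a question about variation in the treatment effect, and a direct answer compares the effects with one another. A separate analysis in each hospital compares each effect with zero. A significant result in one hospital and a non-significant result in the next is not evidence that the two effects differ.

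The trial is sized for one comparison across all 512 women, so each hospital alone has little power. Read against the stated 0.05 threshold, the five results would tend to split by chance. The hospitals are among the likely adopters, and the article offers its results for policy. A message that the ball works in some units and not in others could be acted on, while the generalisability question would remain unanswered.

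**Working it through.** **Inputs from the protocol article.** Five hospitals (Abstract, Methods); total 512, d = 0.25, alpha 0.05, power 0.80, equal arms (Sample size); two-sided testing (Statistical methods); four primary outcomes, namely VAS change, APS-POQ modified, c-LAS and SSQ (Table 1 and Statistical methods).

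**Assumptions.** Hospital sizes are not given, so equal sizes are taken first and then varied. Arms are taken as balanced within each hospital.

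**1. The plan's own figure.** For two means with SD = 1, n per arm = 2 × (1.960 + 0.842)² / 0.25² = 251.2, so 252 per arm (504 in total). The noncentral t calculation gives 253 per arm (506). Rounding to 64 per arm in each of four strata gives 64 × 4 × 2 = 512, with power of about 81%. The stated size reproduces, and it serves the overall comparison.

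**2. Power within one hospital.** 512 / 5 = 102.4 women, or 51.2 per arm. The expected z is 0.25 × √(51.2 / 2) = 1.265. Power is Φ(1.265 − 1.960) = 24.4%, or 24.0% with the t distribution. The smallest d detectable with 80% power is 0.56, more than twice the planning effect.

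Power at d = 0.25 for other assumed hospital sizes:

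| Women in hospital | Power |
|---|---|
| 60 | 16% |
| 80 | 20% |
| 120 | 27% |
| 150 | 33% |
| 200 | 42% |

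**3. Chance of a mixed picture when the effect is the same everywhere.** With d = 0.25 in all five equal hospitals and power 0.240 each:

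- none significant: 0.760⁵ = 0.253
- all significant: 0.240⁵ = 0.001
- some significant and some not: 1 − 0.253 − 0.001 = 0.746, about 75%

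This barely depends on equal sizes. With assumed sizes of 200, 150, 60, 60 and 40 (510 women), the powers are 0.421, 0.331, 0.159, 0.159 and 0.120. The chance that none is significant is 0.579 × 0.669 × 0.841 × 0.841 × 0.880 = 0.241. The chance that all are is below 0.001. A mixed result then has a chance of about 76%.

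**4. Chance of at least one false positive when there is no effect.**

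- One outcome, five hospitals: 1 − 0.95⁵ = 22.6%.
- Four outcomes in each of five hospitals, all independent: 1 − 0.95²⁰ = 64.2%.
- The same 20 tests with an assumed correlation between the outcomes of 0.3, 0.5, 0.7 or 0.9 (simulated): about 62%, 57%, 50% or 39%.

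**5. Power of the alternative.** Take assumed site effects of 0, 0.125, 0.25, 0.375 and 0.5 in five equal hospitals. The squared deviations from the mean of 0.25 sum to 0.15625. The variance of each hospital effect is 2 / 51.2 = 0.0391, so the noncentrality is 0.15625 / 0.0391 = 4.0. The 4-df interaction test then has about 32% power.

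**The case against.** The strongest objection is that one sentence in the Discussion fixes very little. It names no test, outcome or decision rule, and would also fit descriptive hospital estimates. An article may leave such detail to an analysis plan, which is not shown here and may contain an interaction test. This stands in part: the article can be said to state no interaction test, but not to have ruled one out. Nor can hospital be said to be excluded from the final model, since alternative models are foreseen. The point survives because the article does choose a form of analysis, by hospital, for a problem it raises itself, and that form does not address the problem. The one threshold it gives, "value of 0.05 or less is considered statistically significant", carries no exception for subgroups.

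The subgroup sentence is also not the only response to site differences. Training at all sites comes before it and may reduce the variation, although it does not measure what remains.

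A reader might infer a 64% chance of a spurious finding from the hospital analyses. The article does not support that. Five analyses of one outcome give 23%. The 64% needs all four primary outcomes tested in every hospital, no true effect on any of them, and independence between outcomes measured in the same women. The article specifies no such set of 20 tests. The figure is at most an upper limit, and it should not be set beside the 24% power as if both described one scenario: the power assumes a true d of 0.25 on VAS, the 64% no effect at all.

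Finally, the interaction test is weak too. That is correct, and it is why estimates with intervals should carry the main weight.

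**Conclusion.** The concern holds in a limited form. Separate hospital analyses, as stated, do not test whether the effect differs by site. With five equal hospitals each has about 24% power at d = 0.25, and assumed sizes of 60 to 200 women give about 16% to 42%. Under a common effect of that size, a split between significant and non-significant hospitals has a chance of about 75%. With no effect, the chance of at least one false positive is about 23% for one outcome, rising to at most about 64% only under the 20-test conditions above.

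These figures rest on assumed hospital sizes, balanced arms within hospitals, and results being read against the 0.05 threshold. A reader might also infer that the main result is compromised. It is not: the overall comparison of 512 women is unaffected by this point, which concerns how site results are interpreted. The change is worth making because it is cheap and the stated analysis would probably mislead.

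**What to change.** Replace the separate hospital analyses with one hospital-by-arm interaction term, or a random arm-by-hospital variance, in the main model for the VAS outcome. Show the hospital effects in a forest plot with 95% confidence intervals, label them exploratory, and give no within-hospital P values. If the analysis plan already contains such a test, align the sentence in the Discussion with it.

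The cost is wording in the analysis plan; no new data are needed and trial conduct does not change. There are two downsides. Individual hospitals get no significance statement of their own. The interaction test has low power (about 32% for assumed site effects spread from 0 to 0.5), so the plan should say that a non-significant interaction is not proof of a uniform effect.
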